## **Intervention**

Participants are randomly allocated to either treatment (glucocorticoid) group or placebo (saline) group. Each group will receive two injections at baseline: one is the glucocorticoid or saline into IPFP, and the other is intra-articular hyaluronic acid as a background treatment.

The product of the glucocorticoid is betamethasone injectable suspension (Diprosone) and the dosage is 1 ml. To alleviate the discomfort on local tissues, the suspension injected into the IPFP will be pre-mixed with 0.5 ml saline and 0.5 ml lidocaine (concentration: 2%). That is, the total amount of the drug injected into the IPFP for the glucocorticoid group will be 2.0 ml. Accordingly, a total of 2.0 ml drug including 1.5 ml saline and 0.5 ml lidocaine will be injected into the IPFP in the placebo group. The injection of glucocorticoid or placebo into the IPFP will be performed under the guidance of ultrasonography. The procedures are as follows: 1) the participant lies on the bed with a small pillow behind his/her knee to bend the knee joint by 20-30°; 2) the ultrasonic probe is placed under the patella to show the IPFP and its inflammatory sites (figure 1); 3) insert the needle through the inferior lateral patella; 4) the drug is injected on two sites at the bottom of IPFP near the synovium where synovial hyperplasia is obvious, with a dosage of 1 ml at each site. All physical therapists will be trained for this injection under the supervision of an experienced therapist.

The intra-articular hyaluronic acid (ARTZ, Seikagaku Corporation, Japan) injection will be added as a background treatment. That is, after completing the process

of IPFP injection, the participants in both groups will receive 2.5 ml hyaluronic acid suspension injection through the suprapatellar bursa into the intra-articular space under the guidance of ultrasonography.

## Outcome measures

An overview of the data collection is listed in Table 1. All questionnaires (VAS, WOMAC, four-dimensional Assessment of Quality of Life: AQoL-4D, and nine-items Patient Health Questionnaire: PHQ-9) and queries about pain medication use and the use of medication & supplements will be applied at baseline, 4, 8, and 12 weeks follow-ups. MRI assessments including effusion-synovitis volume, Hoffa-synovitis score, tibiofemoral bone marrow lesion maximum size, tibiofemoral cartilage defects, and IPFP volume will be examined at baseline and 12 weeks follow-up. Other measures including demographic data, clinical evaluation and history collection, ultrasonographic examination in the study knee, and effusion-synovitis score assessed by MRI will be recorded at baseline/screening only.

**Table 1. Schedule of data collection**

|                                               | Screening/
Baseline | 4 weeks* | 8 weeks* | 12 weeks |
|-----------------------------------------------|------------------------|----------|----------|----------|
| Primary outcomes                       |                        |          |          |          |
| Knee pain (VAS)                               | ✓                      | ✓        | ✓        | ✓        |
| Effusion-synovitis volume #        | ✓                      |          |          | ✓        |
| Secondary outcomes                     |                        |          |          |          |
| WOMAC                                         | ✓                      | ✓        | ✓        | ✓        |
| Hoffa-synovitis score #
(MOAKS) | ✓                      |          |          | ✓        |
| Quality of life (AQoL-4D)                     | ✓                      | ✓        | ✓        | ✓        |
| Pain medication use                           | ✓                      | ✓        | ✓        | ✓        |
| infrapatellar fat pad volume #     | ✓                      |          |          | ✓        |

|                                                           |   |   |   |   |
|-----------------------------------------------------------|---|---|---|---|
| Adverse reaction                                          |   | ✓ | ✓ | ✓ |
| Other measures                                     |   |   |   |   |
| Demographic data †                             | ✓ |   |   |   |
| Clinical evaluation § and history collection   | ✓ |   |   |   |
| Ultrasonographic examination in the study knee            | ✓ |   |   |   |
| Effusion-synovitis score # (MOAKS)             | ✓ |   |   | ✓ |
| Tibiofemoral bone marrow lesion maximum size # | ✓ |   |   | ✓ |
| Tibiofemoral cartilage defect #                | ✓ |   |   | ✓ |
| Use of medication & supplements                           | ✓ | ✓ | ✓ | ✓ |
| Adverse events                                            |   | ✓ | ✓ | ✓ |
| Depression (PHQ-9)                                        | ✓ | ✓ | ✓ | ✓ |

VAS: visual analogue scale; WOMAC: Western Ontario and McMaster Universities Osteoarthritis Index; MOAKS: MRI Osteoarthritis Knee Score; AQL-4D: four-dimensional Assessment of Quality of Life; PHQ-9: nine-items Patient Health Questionnaire.

\* The participants will complete the questionnaires (VAS, WOMAC, AQL-4D, an PHQ-9) of the follow-ups at home and send back to researchers. As for pain medication use, use of medication & supplements, and adverse events, the researchers will ask the participants via remote interview.

# In MRI.

† Including names, gender, birth date, height, weight and contact details.

§ Diagnosis of symptomatic knee osteoarthritis according to American College of Rheumatology criteria.

## Questionnaires and queries

The VAS (100 mm visual analog scale) will be used to assess knee pain using the standard question: “On this line, how would you rate your knee pain in the last week?”. A higher score indicates a higher level of pain severity.

The WOMAC requires patients to rate their pain (five items), stiffness (two items), and functional dysfunction (17 items) in the last week. Each item is a 100-mm visual analog scale. The WOMAC score is calculated by summing the score of each

item with every 1 mm representing one point. A higher WOMAC score indicates a more severe OA symptom. When more than five items are not completed, the WOMAC score would be regarded as missing data. Otherwise, the WOMAC score would be calculated by averaging the remaining score and then multiplying by 24.

The AQL-4D will be used to assess the quality of life in the last week. It comprises four dimensions of independent living, social relationships, psychological well-being, and physical senses. Each dimension has three items with four response categories ranging from 0-3. The total AQL-4D score ranges from 0-36, and a higher score indicates a lower quality of life.

The PHQ-9 will be used to assess the depression in the last two weeks. It comprises nine items with four response categories scored from 0-3. The total PHQ-9 score ranges from 0-27, and a higher score indicates a more severe depression level.

Queries about medications and supplement use will also be recorded at baseline and each follow-up. Adverse events and reactions will be recorded at each follow-up. Pain medication use would be determined by the researchers from the records of medication use. Adverse events are defined as any untoward event occurring during the trial, regardless of its relation to treatment, and they need to be reported spontaneously when they occur. Details of the adverse event will be recorded and whether it is an adverse reaction will be determined.

## **MRI assessments**

Sagittal images on intermediate-weighted/proton density-weighted fat suppression sequences will be used in assessing effusion-synovitis volume/score, Hoffa-synovitis score, tibiofemoral bone marrow lesion maximum size, tibiofemoral cartilage defects, and IPFP volume.

Effusion-synovitis volume will be calculated by summing the volume of effusion synovitis in suprapatellar pouch, central portion, posterior femoral recess, and submuscular recess using OsiriX software. Effusion-synovitis score was scored using MOAKS which can be divided into 0-3 grades.

Hoffa-synovitis score (MOAKS method) will be assessed according to the discrete area with increased signal intensity in the IPFP on MRI images. It can be divided into 0-3 grades: grade 0=normal, grade 1=IPFP with an increase of signal intensity of <10%, grade 2=IPFP with an increased signal intensity between 10% and 20%, grade 3=IPFP with an increase in signal intensity of >20%.

Tibiofemoral bone marrow lesions are defined as discrete areas of increased signal in the subchondral bone. Bone marrow lesions maximum size will be assessed at the medial tibial, medial femoral, lateral tibial, and lateral femoral compartments. Slice with the greatest area of bone marrow lesions in a specific compartment will be chosen to assess bone marrow lesions' maximum size of the corresponding compartment. Bone marrow lesions on adjacent slices will be measured and compared to locate the slice with the maximum lesion size. Tibiofemoral bone marrow lesions' maximum size will be calculated by summing the maximum lesions' size of the four compartments.

Cartilage defects will be graded using a modified Outerbridge classification as follows: grade 0=normal, grade 1=focal blistering and intra-cartilaginous hyperintensity with a normal contour, grade 2=irregularities on the surface and loss of thickness of less than 50%, grade 3=deep ulceration with loss of thickness of more than 50% without exposure of subchondral bone, grade 4=full-thickness chondral wear with exposure of subchondral bone. Cartilage defects will be assessed at the medial tibial, medial femoral, lateral tibial, and lateral femoral compartments, and tibiofemoral cartilage defects will be obtained by summing the scores of the four compartments.

IPFP volume will be measured by manually drawing disarticulation contours around the IPFP boundaries using OsiriX software as reported previously.

## **Data management**

Research Electronic Data Capture (REDCap), a secure web-based application, will be applied to facilitate the data collection throughout the study. It has a function of self-monitoring in data entry which maximizes data quality. After each follow-up, the researcher will timely input the obtained data into REDCap, and a backup REDCap

data will be regularly stored at the principal study center. At the completion of the follow-up, the MR images will be assessed. After all the data are obtained, unblinding will be undertaken. In this trial, the two-step unblinding method will be applied. In the first step of unblinding, the participants will be classified into group A and group B for data analyses. After that, the second step of unblinding will assign the two groups to the treatment group or placebo group.

The participants are allowed to withdraw at any time throughout the study. If the participants withdraw from the study before the end of the trial, they are asked to have data collected including MRI assessment. The reason and date of the withdrawal will be recorded and the data before the withdrawal will be asked to retain.

## **Sample size**

We estimated the sample size based on the primary outcomes. The formula  $n_1=n_2=2 \times [(Z_\alpha+Z_\beta) \times \sigma/\delta]^2$  was used to calculate the sample size with an  $\alpha$  level of 0.05 (two-sided;  $Z_\alpha=1.96$ ) and a power of 80% ( $Z_\beta=0.842$ ). It is reported that the minimum clinically important difference (MCID) of knee VAS pain in people with knee OA is 19.9 mm. Assuming that the knee VAS pain reduction in the glucocorticoid injection group compared with the saline injection group is clinically significant, the difference between knee VAS pain changes of the two groups should be at least 19.9 mm ( $\delta$ ). As the standard deviation of the change in knee VAS pain from baseline to three months follow-up is 24.2 mm ( $\sigma$ ) in our previous trial, the  $n_1=n_2$  calculated is 24. Considering a 20% loss to follow-up, a sample size of 30 patients in each group is needed.

As an MCID for effusion-synovitis volume has not yet been defined, the detectable difference of effusion-synovitis volume between the treatment and placebo groups were calculated based on the given sample size ( $n_1=n_2=30$ ) and  $\sigma$ . According to the standard deviation of the change in effusion-synovitis volume from baseline to 12 weeks follow-up being 7.69 ml ( $\sigma$ ) in the same previous trial, the detectable difference of effusion-synovitis volume calculated is 6.22 ml.

## Statistical plan

Baseline characteristics will be displayed in descriptive statistics according to the data type. Continuous variables with normal distribution will be displayed by means and standards deviation. Continuous variables with non-normal distribution will be displayed by median and interquartile range. Category variables will be displayed by proportion.

The intention-to-treat analysis will be the primary analyses method. The per-protocol analysis will be the second analyses method where the per-protocol population is defined as participants completed four follow-ups without major protocol deviations. There is no interim analysis in this research. Missing data due to dropout and nonresponses will be addressed using multiple imputations with chain equations. For each treatment group, imputations will be performed separately based on the baseline characteristics and the non-missing values at other time points of the missing variables with the assumption of data missing at random. Imputations will be performed separately for each treatment group and each outcome using baseline variables of age, sex, BMI, and study site and non-missing values of the outcomes at baseline and each follow-up with the assumption of data missing at random.

Mixed-effects regression models will be used to calculate treatment group differences with continuous measures. In the models, fixed effects will be follow-up time, baseline covariates (including age, sex, BMI, baseline value of the corresponding outcome), treatment, and interactions between follow-up time and baseline covariates and treatment. Study site and individual participant identification will be treated as the random intercepts and follow-up time as the random slop in the models. The overall treatment group differences will be calculated by the linear combination of the estimated coefficients. Wilcoxon rank-sum test will be used to analyze the difference in pain medication use between the treatment and placebo groups. Pain medication use will be classified as commenced/increased, unchanged, or discontinued/decreased. The chi-square test or Fisher's exact test will be used to compare the incidence of adverse reactions between the two treatment groups, and the number of adverse reactions will

be reported as the number of participants reporting at least one adverse reaction. All analyses will be performed using Stata, version 15 (StataCorp). A 2-sided  $P$  value of 0.050 will be treated as statistically significant.

## Abbreviations

OA: osteoarthritis; IPFP: infrapatellar fat pad; MRI: magnetic resonance imaging; VAS: visual analogue scale; WOMAC: Western Ontario and McMaster Universities Osteoarthritis Index; MOAKS: MRI Osteoarthritis Knee Score; AQoL-4D: four-dimensional Assessment of Quality of Life; PHQ-9: nine-items Patient Health Questionnaire; REDCap: Research Electronic Data Capture; MCID: minimum clinically important difference.

## Audits and steering

The Trial Steering Committee will meet PIs to review the trial conduct every 3 months. Each electronic case report form will be checked by a research coordinator for completion. This committee's task is to ensure the trial follows the study plan. As it is a low-risk intervention trial, a Data Monitoring Committee is not considered.

## Protocol amendments

In case of any protocol amendments, the amended protocol will be submitted to Clinical Trial Governance Committee and Ethical Committee for approval. Each PI of the study center will then be notified for the amendments. A copy of the revised protocol will be added to the Investigator Site File. The amendments will be recorded in ClinicalTrials.gov. Any deviations from the protocol will be fully documented using a breach report form.

### 1.3. Abbreviations

GLucocorticoid injections into InfrapaTellar faT pad in patients with knee osteoarthritis (GLITTERS), Statistical analysis plan (SAP), osteoarthritis (OA), infrapatellar fat pad (IPFP), Visual Analogue Scale (VAS), Western Ontario and McMaster Universities Osteoarthritis Index (WOMAC), Research Electronic Data Capture (REDCap), Assessment of Quality of Life-4 Dimensions (AQoL-4D), and Patient Health Questionnaire-9 (PHQ-9), adverse event (AE), magnetic resonance imaging (MRI), minimum clinically important difference (MCID).

## **2. Introduction**

### **2.1. Background and rationale**

Inflammatory phenotype is one of the most typical phenotypes of knee osteoarthritis (OA). Infrapatellar fat pad (IPFP) and synovium as a structural complex are considered as the main source of inflammation in knee OA. Glucocorticoid is a traditional anti-inflammatory drug for knee OA. Clinically, intra-articular glucocorticoid injections are recommended for people with knee OA to reduce their pain. However, emerging evidence has shown that repeated intra-articular injections over 2 years would induce more cartilage loss. Thus, the injection of glucocorticoid into IPFP may not only play a better role in anti-inflammatory but minimize cartilage deterioration among inflammatory knee OA patients. To date, there is no study about the injection of drugs into IPFP. Therefore, we hypothesized that the IPFP injection of glucocorticoid can effectively reduce the knee pain and effusion-synovitis volume, compared to the placebo injection among people with symptomatic knee OA who have effusion- and Hoffa-synovitis.

### **2.2. Objectives**

- Primary aim: to assess whether the injection of glucocorticoid into the IPFP can effectively reduce the knee pain measured by visual analogue scale (VAS) and MRI measured effusion-synovitis volume, compared to the placebo injection among patients with symptomatic knee OA who have both effusion- and Hoffa-synovitis.
- Secondary aims: to evaluate whether the injection of glucocorticoid into the IPFP effectively reduces the total Western Ontario and McMaster Universities Osteoarthritis Index (WOMAC) score, MRI-assessed Hoffa-synovitis score,

and pain medication use; improves the quality of life; and has a difference in IPFP volume and adverse reaction, compared to the placebo injection among symptomatic knee OA patients with both effusion- and Hoffa-synovitis.

### **3. Study methods**

#### **3.1. Trial design**

GLucocorticoid injections into InfrapaTellar faT pad in patients with knee osteoarthritis (GLITTERS) is a multicentre, randomized, double-blind, placebo-controlled trial over 12 weeks. Participant recruitment is conducted across four centres: Zhujiang Hospital of Southern Medical University, the Sixth Affiliated Hospital of Sun Yat-sen University, the Third Affiliated Hospital of Sun Yat-sen University, and Beihai People's Hospital. This study will use competitive enrolment.

#### **3.2. Randomization and blinding**

Using block randomization in block size of four, eligible participants in each centre will be assigned to the treatment or placebo group with a 1:1 allocation rate based on computer-generated random numbers. A staff member who is not involved in this trial will pack the drugs with a random number indicated on each of the packages. Allocation concealment will be ensured and Allocation results will be not revealed until the completion of final data analyses. Double-blind (participants & researchers including outcome assessors and statisticians) design will be applied in this trial. Because of the different appearance of the injection drugs, the physical therapists for the injections are not blinded, and they will not be involved in other processes of this trial. During the period of preparing and injecting the drug, participants will be out of sight of the injection drugs. Unblinding will be conducted after all the data analyses are obtained. Emergency unblinding will be permissible when a serious adverse event (AE) happens, and patients who are unblinded will be withdrawn from the trial.

#### **3.3. Sample size estimation**

We estimated the sample size based on the primary outcomes. The formula  $n_1=n_2=2 \times [(Z_\alpha+Z_\beta) \times \sigma/\delta]^2$  was used to calculate the sample size with an  $\alpha$  level of 0.05 (two-sided;  $Z_\alpha=1.96$ ) and a power of 80% ( $Z_\beta=0.842$ ). It is reported that the minimum clinically important difference (MCID) of knee VAS pain in people with knee OA is 19.9 mm. Assuming that the knee VAS pain reduction in the glucocorticoid injection

group compared with the saline injection group is clinically significant, the difference between knee VAS pain changes of the two groups should be at least 19.9 mm ( $\delta$ ). As the standard deviation of the change in knee VAS pain from baseline to three months follow-up is 24.2 mm ( $\sigma$ ) in our previous trial, the  $n_1=n_2$  calculated is 24. Considering a 20% loss to follow-up, a sample size of 30 patients in each group is needed.

As an MCID for effusion-synovitis volume has not yet been defined, the detectable difference of effusion-synovitis volume between the treatment and placebo groups were calculated based on the given sample size ( $n_1=n_2=30$ ) and  $\sigma$ . According to the standard deviation of the change in effusion-synovitis volume from baseline to 12 weeks follow-up being 7.69 ml ( $\sigma$ ) in the same previous trial, the detectable difference of effusion-synovitis volume calculated is 6.22 ml.

### **3.4. Timing of final analysis**

After receiving SAP approval from Zhujiang Hospital's Clinical Research Centre and completing data collection, we will initiate data cleaning and validation. Subsequent to these procedures, the final analysis will be executed.

### **3.5. Timing of outcome assessment**

Upon completion of the MRI follow-up assessments for all participants, the evaluation will proceed with MRI assessments. We will utilize sagittal images obtained from intermediate-weighted/proton density-weighted fat suppression sequences for the quantification and scoring of effusion-synovitis volume/score, Hoffa-synovitis score, tibiofemoral bone marrow lesion maximum size, tibiofemoral cartilage defects, and IPFP volume.

Data from questionnaires, including VAS, WOMAC, AQL-4D, and PHQ-9, as well as information on medication and supplement use, AEs, and adverse reactions, will be systematically documented and managed via the Research Electronic Data Capture (REDCap) system at each visit. This tool is a secure, web-based software designed specifically for research data management, featuring: (1) a user-friendly interface for accurate data entry; (2) comprehensive audit trails for monitoring data alterations and exports; (3) automated export functions for efficient data transfer to popular statistical analysis software; and (4) capabilities for integrating data from external sources. Additionally, backups of de-identified data will be securely stored in password-protected electronic formats.

## **4. Statistical Principles**

### **4.1. Confidence Intervals and *P*-values**

A 2-sided *P* value of 0.050 will be treated as statistically significant. Given the lack of correlation between the two primary outcomes, which reflect distinct aspects of OA symptom and structural changes, we will refrain from adjusting the *P*-value for multiplicity in their analysis.

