## **6. Analysis**

### **6.1. Outcome definition**

- Primary outcomes: changes in knee pain as assessed by the VAS and effusion-synovitis volume measured on MRI.
- Secondary outcomes: changes in the total score of WOMAC, MRI-detected Hoffa-synovitis score, quality of life measured using AQoL-4D, pain medication use, IPFP volume, and the incidence of adverse reactions.

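### SAP 4.1 leaves two primary outcomes unadjusted because they are said to be uncorrelated, which is where inflation is largest, and no rule says whether one or both must succeed

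*Combined protocol and SAP*

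**What the plan says.** SAP 6.1 defines the primary outcomes as "changes in knee pain as assessed by the VAS and effusion-synovitis volume measured on MRI". The primary aim in SAP 2.2 is to find out whether the injection can "reduce the knee pain measured by visual analogue scale (VAS) and MRI measured effusion-synovitis volume"; the protocol's Objectives section joins the two outcomes in the same way.

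On significance, the protocol's Statistical plan says that a two-sided P "value of 0.050 will be treated as statistically significant". It does not mention multiplicity. SAP 4.1 repeats the threshold, declines any multiplicity correction, and gives the only justification in either document: "Given the lack of correlation between the two primary outcomes, which reflect distinct aspects of OA symptom and structural changes, we will refrain".

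The sample size (protocol, Sample size; SAP 3.3) uses an alpha "level of 0.05 (two-sided") and 80% power, applied to VAS pain. For effusion-synovitis volume the documents give only a detectable difference, because no MCID has been defined. Neither document contains a success rule, a testing order, an alpha split or an estimate of the correlation between the two outcomes.

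**The concern.** SAP 4.1 rests the lack of adjustment on "Given the lack of correlation between the two primary outcomes". Correlation between outcomes is what makes two tests partly redundant and so limits the extra false positives. Without it, the second test adds close to a full second chance of error. The premise, if true, is therefore a reason for adjusting.

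The premise is also unsupported. No estimate is given, and the introductions to both documents present pain and effusion-synovitis as targets of one anti-inflammatory action. The protocol's reference list includes a study whose title concerns associations between effusion-synovitis and knee pain in older adults. A title gives no size, but it does not suggest that zero is a safe assumption.

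At stake is how the main conclusion is reached. With two results and no rule, a reader cannot tell in advance what would make the trial positive, and that choice could be made once the results are known.

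**Working it through.** **Inputs.** Two primary outcomes (SAP 6.1). Two-sided 0.05 per test (protocol, Statistical plan; SAP 4.1). From SAP 3.3: Z values 1.96 and 0.842; "the difference between knee VAS pain changes of the two groups should be at least 19.9 mm"; "standard deviation of the change in knee VAS pain from baseline to three months follow-up is 24.2 mm"; 20% loss to follow-up. There is no interim analysis (SAP 6.2), so no other alpha is spent that way. The correlation r between the two test statistics is not given and is varied as an assumption.

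**1. The plan's own figure.** n per arm = 2 × [(1.96 + 0.842) × 24.2 / 19.9]² = 23.2, rounded up to 24. Allowing for 20% loss, 24 / 0.8 = 30. Both figures reproduce, and both are for VAS pain at an unadjusted 0.05.

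**2. If either outcome suffices.** With both nulls true and independent tests, the chance of at least one false positive is 1 − 0.95² = 0.0975. For jointly normal two-sided tests it is P(|Z1| > 1.96 or |Z2| > 1.96):

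| r | At least one false positive |
|---|---|
| 0 | 9.75% |
| 0.3 | 9.5% |
| 0.5 | 9.1% |
| 0.7 | 8.3% |
| 0.9 | 7.0% |

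Negative r gives the same values. The maximum is at r = 0, the case that the SAP invokes.

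These figures count errors in both directions. False claims of benefit alone, at r = 0, are 1 − 0.975² = 4.94%, against 2.5% for a single outcome.

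**3. If both outcomes are required.** With both nulls true and r = 0, the error is 0.05² = 0.25%. If only one null is true it cannot exceed 5%, because that test must itself reject. Error is controlled without adjustment.

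Power then becomes the issue. If each outcome has exactly 80% power, joint power is 0.80 × 0.80 = 64% at r = 0 and 69% at r = 0.5 (bivariate normal, mean 2.802 on each statistic).

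That figure depends on retention and on the volume effect. Taking the VAS mean at a given n, (19.9 / 24.2) × √(n/2), and assuming the same standardized effect for volume, joint power for r = 0 to 0.5 is:
- 24 evaluable per arm (mean 2.849): 66% to 70.5%
- 30 evaluable per arm (mean 3.185): 79% to 82%

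**4. Price of an equal alpha split.** At 0.025 per outcome (Z = 2.2414), VAS pain needs 2 × [(2.2414 + 0.842) × 24.2 / 19.9]² = 28.1, so 29 evaluable per arm, and 29 / 0.8 = 36.25, so 37 randomized. At the planned numbers, VAS power would fall from 81.3% to 72.8% with 24 evaluable per arm, and from 89.0% to 82.7% with 30. The error at r = 0 would be 1 − 0.975² = 4.94%.

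**The case against.** The best defence is in the same sentence of SAP 4.1, which also says that the outcomes reflect distinct aspects of disease, one symptomatic and one structural. Some trialists accept unadjusted testing when each outcome answers its own question and is reported on its own terms. That position is respectable, but it does not depend on correlation, and the plan does not follow it through. It states one joint hypothesis and one joint primary aim, and nowhere says that two separate conclusions will be drawn without an overall claim.

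Three stronger readings are tempting, and the documents do not support them.

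- A reader might infer that the trial's error rate is 9.75%. That needs an either-outcome rule and both nulls true. No such rule is written, and the primary aim's wording is compatible with requiring both.
- A reader might infer that the plan breaks a promised 5% trial-level rate. It promises none: 0.05 is the per-test threshold and the sample-size alpha, and the decision not to adjust is openly disclosed.
- A reader might infer that requiring both outcomes contradicts the stated 80% power. That power is stated for VAS pain alone and is unaffected. Joint power is never claimed, and 64% is only its value when each outcome has exactly 80% and r = 0.

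What stands from the defence is that separate claims are a legitimate choice and that a fixed sequence is one valid rule among several. It does not rescue the correlation argument or supply the missing rule.

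**Conclusion.** The point holds in conditional form. The stated reason for not adjusting is backwards, and the success rule is absent. If either outcome can make the trial positive and both nulls are true, the chance of at least one false positive is 9.75% at zero correlation, falling to 8.3% at r = 0.7. If both are required, error is at or below 5%, and the gap is that the sample size was not set for joint success.

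The 9.75% maximum assumes jointly normal two-sided statistics; under arbitrary dependence the bound is 0.05 + 0.05 = 10%. This should be corrected because it governs the trial's main conclusion and cannot credibly be settled after the results are seen.

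**What to change.** Delete the lack-of-correlation rationale from SAP 4.1. State one decision rule there and in the protocol's Statistical plan that holds the familywise error at 5%. Because the protocol's Data management section provides for analysis by coded groups A and B before the codes are broken, the rule should be fixed before the first unblinding step; two-sided P values are visible from coded groups.

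**Preferred rule: fixed sequence.** Test VAS pain first at two-sided 0.05. Test effusion-synovitis volume at two-sided 0.05 as confirmatory only if VAS pain is significant; otherwise report volume with its 95% CI and no confirmatory claim. VAS pain is the natural first test because it has the MCID and drives the sample size.

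**Cost.** Wording only. VAS pain keeps the full 0.05, so 24 evaluable and 30 randomized per arm stand. The downside is that no confirmatory volume claim is possible if VAS pain fails. A confirmatory volume result needs both tests to succeed, so it carries the joint power shown above.

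**Acceptable alternatives.**
- A Holm procedure, which keeps the outcomes on an equal footing but starts at 0.025 for the smaller P value.
- Requiring both outcomes, with joint power reported.

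If the sponsor prefers two separate unadjusted claims because the outcomes address distinct aspects, the SAP should say so. It should state that no overall trial-success claim will be made on either outcome alone, and acknowledge the error of up to 9.75%.
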